#### Treatment fidelity and process

Research assistants are tracking the number of newsletters sent. At the 12-month assessment, participants are also asked to report on the frequency they received and read newsletters; they also complete a questionnaire to rate the usefulness and satisfaction with Fit Moms/*Mamás Activas* content and its delivery, which includes ratings of various aspects of the program. In the intervention group, data (via background website monitoring) are also available on the number of logins and number of online self-monitoring records completed, frequency of posting to the message boards, viewing of video resources, redemption of diaper points, and page views for various website features. Attendance at monthly group meetings is also tracked. All group treatment sessions are audiotaped, and a random 20% of these sessions are being reviewed by an interventionist who did not conduct the intervention session. The reviewer listens to the session tape and completes a fidelity checklist developed specifically for this trial to confirm that the essential content for each session is being covered.

#### Cluster-level assessment

Basic demographic information and lactation status is collected in all women in the WIC. In addition, we are assessing any changes to each clinic’s nutrition and physical activity programs and documenting any external independent programmatic policy and environmental changes. Data are collected annually related to levels of physical activity and nutrition that may affect women in the WIC, including: (1) aspects of the environment in the clinic and surrounding neighborhood (such as the promotion of walking programs); (2) relevant grants and research program initiatives at clinics; (3) local, state, or federal mandates; and (4) promotions and advertising.

#### Procedures to retain sample

Clinic retention strategies include maintaining ongoing contact with state, county, and local WIC agencies. At the local level, we provide small incentives and ‘lunch and learn’ sessions to update clinics on study progress. Participant retention strategies have been used effectively in our other studies of multiethnic childbearing women, and include collecting multiple phone numbers and numbers of relatives and friends for contact. For each data collection visit, participants have their visit scheduled by phone, are sent written reminders, and are called the day before. Missed visits are rescheduled and followed up on. Costs for transportation and childcare coverage are provided to participants with repeat missed assessments. If necessary, assessments are completed at patients’ homes. Compensation is provided to further promote retention: US$25 for completing the baseline and six-month assessments and US$50 for the 12-month assessment.

#### Sample size calculation

The targeted sample size (12 clinics; 34 participants per clinic; total N = 408) is projected to provide ≥80% power to detect a meaningful difference in weight change at 12 months as small as 2 kg between group means, when the standard deviation is 4.5 kg and the intraclass correlation (ICC) is 0.02, using a two-sided *t*-test with a significance level of 0.05, and accommodating anticipated rates of loss to follow-up (30% participant attrition at 12 months). Although we do not anticipate clinic attrition, 10 clinics (five in each condition) would provide 80% power to detect a difference in weight change as small as 2 kg. An ICC of 0.002 was estimated from results of our pilot demonstration trial and a WIC survey study [130], but we have conservatively used an ICC of 0.02 for sample size calculations [131]. For secondary aims, in our most conservative estimates [25], we would have greater than 80% power to detect both medium and large effects (Cohen’s d = 0.5 and 0.8, respectively) for any continuous or categorical outcome variable at the alpha = 0.05 level using a two-sided test of significance.

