### Study aims

Fit Moms/*Mamás Activas* is a cluster randomized clinical trial funded by the National Institute of Diabetes, Digestive, and Kidney Diseases (NIDDK). The clinical site is at California Polytechnic State University, San Luis Obispo ([name], Principal Investigator (PI)) and an additional performance site that is overseeing development and delivery of the online and text-messaging intervention is the University of North Carolina at Chapel Hill ([name], PI). In this cluster randomized trial, 12 WIC clinics are randomized to receive the standard WIC program for 12 months or the enhanced WIC plus internet-based postpartum weight loss program. The primary hypothesis is that the enhanced WIC plus internet postpartum weight loss program will produce significantly greater weight losses than the standard WIC at six and 12 months.

Secondary aims will determine whether the enhanced WIC plus internet postpartum weight loss program will result in greater improvements in eating and exercise behaviors (examined at 0, six, and 12 months) and psychosocial parameters (depression, social support, self-efficacy, body image, and stress) than standard care. The study will examine the proportion of women who achieve pre-pregnancy weight at six and 12 months and identify baseline characteristics that may moderate the efficacy of the intervention (such as ethnicity, socioeconomic status, pre-pregnancy weight, parity, and breastfeeding status). The study will also examine the relationship between changes in behaviors, psychosocial factors, and weight changes during the 12-month period. These evaluations will help identify the mechanisms by which the intervention produces greater success compared to the standard WIC.

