A secondary aim is to test the hypothesis that the intervention will result in a greater percentage of the women achieving their preconception weight or below at 12 months. For this analysis, a generalized linear mixed-model (binomial with a logit link) will be used for proportion at preconception weight or below at six and 12 months postpartum, including the same predictors described above. For secondary analyses comparing changes in behavioral and psychosocial variables, the effect of treatment at each time point will be investigated using the same basic linear mixed-effects model described above. In analyses of the possible differential effects of treatment on various subgroups of women, interactions between patient-level covariates (as in the main analyses) and group will be examined. A Bonferroni adjustment will be used to adjust for multiple comparisons. Also, generalized linear mixed-model analyses, as described above, will also be conducted to examine whether baseline variables moderate weight loss outcomes. Analyses of whether any effect of the intervention is mediated by differences in demographic, behavioral, and psychosocial factors will be conducted by first eliminating variables that have no impact on weight loss, then variables of interest will be entered into a final linear mixed-effects model, using both theoretical considerations to guide variable selection and the statistical strength of potential predictor variables [140].

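### The power statement for the secondary aims holds for one unadjusted between-group comparison, but its wording also takes in Bonferroni-adjusted moderator interactions, for which power is well below 80%

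*Protocol article*

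**What the plan says.** The sample size section of the protocol article plans for "12 clinics; 34 participants per clinic; total N = 408", allows for "30% participant attrition at 12 months", and adds that "we have conservatively used an ICC of 0.02 for sample size calculations". The primary target is a difference "as small as 2 kg between group means, when the standard deviation is 4.5 kg". It then turns to the secondary aims as a group and says "we would have greater than 80% power to detect both medium and large effects", defined as Cohen's d of 0.5 and 0.8, for any continuous or categorical outcome at two-sided alpha 0.05.

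Under Study aims, the paragraph that opens with the secondary aims goes on to say that the study will "identify baseline characteristics that may moderate the efficacy of the intervention". It gives five examples: ethnicity, socioeconomic status, pre-pregnancy weight, parity and breastfeeding status.

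The Analysis plan says how this will be tested: "interactions between patient-level covariates (as in the main analyses) and group will be examined". The next sentence reads: "A Bonferroni adjustment will be used to adjust for multiple comparisons". The article does not give the number of comparisons, and it does not say whether the adjustment also covers the behavioral and psychosocial outcomes.

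**The concern.** The power sentence and the analysis plan describe different tests at different significance levels. The power sentence describes a two-group contrast at alpha 0.05. A moderator test is a difference of differences. With an even split its variance is about four times that of a main effect when clustering is ignored, and a Bonferroni adjustment brings alpha below 0.05.

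The risk lies in interpretation. A reader who takes the statement to cover all secondary aims could treat a non-significant interaction with, say, ethnicity or breastfeeding status as evidence that the effect is uniform. The trial would in fact often miss a difference in effect of the size that the article calls medium.

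**Working it through.** **Inputs from the sample size section.** 12 clinics, 34 women per clinic, 30% loss, ICC 0.02; primary difference 2 kg with SD 4.5 kg. Equal allocation is assumed.

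- Analysed per clinic: 34 × 0.7 = 23.8. Per arm: 6 × 23.8 = 142.8.
- Design effect: 1 + (23.8 − 1) × 0.02 = 1.456.
- Standard error of a between-group difference in SD units: √(2 × 1.456 / 142.8) = 0.1428.

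**Step 1: primary figure, as a check on the method.** 2/4.5 = 0.444 and 0.444/0.1428 = 3.11. Power is 80.1% by noncentral t on 12 − 2 = 10 df and 87.5% by normal approximation. Both agree with the stated 80% or more.

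**Step 2: the secondary figure as stated.** For d = 0.5, 0.5/0.1428 = 3.50. Power at alpha 0.05 is 88.3% (t, 10 df) or 93.8% (normal). For d = 0.8 it exceeds 99% either way. The stated figure reproduces.

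**Step 3: a moderator interaction.** Assume a binary participant-level moderator with share p in one category, similar in every clinic. The clinic effect then largely cancels, leaving a variance factor of 1 − ICC = 0.98:

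SE = √(0.98 × [2/(142.8p) + 2/(142.8(1 − p))])

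This is 0.234 for p = 0.5 and 0.293 for p = 0.2. Power = Φ(δ/SE − z), with z = 1.960 at alpha 0.05 and 2.576 at 0.05/5 = 0.01.

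| Interaction δ | Alpha | 50/50 split | 20/80 split |
|---|---|---|---|
| 0.5 SD | 0.05 (unadjusted) | 57% | 40% |
| 0.5 SD | 0.01 (five moderators) | 33% | 19% |
| 0.8 SD | 0.01 (five moderators) | 80% | 56% |

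The 57% is the most favourable case for a binary moderator under these inputs: even split, no adjustment, and the smaller variance factor. With the full design effect (1.456 in place of 0.98), the even-split figures for 0.5 SD are 42% unadjusted and 21% at alpha 0.01. If Bonferroni ran over the roughly 17 covariates listed in the analysis plan, they would be 20% (even split) and 10% (20/80 split). With no loss to follow-up at all, the even-split figures would be 72% unadjusted and 49% over five.

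The interaction detectable with 80% power at alpha 0.01 is (2.576 + 0.842) × SE. That is 0.80 SD for an even split and 1.00 SD for a 20/80 split. On the weight scale, 0.80 × 4.5 = 3.6 kg, against the 2 kg for which the trial was sized.

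**Step 4: only if the Bonferroni sentence also covers the secondary outcomes.** A between-group d = 0.5 at alpha 0.01 (five outcomes) has 63% power (t, 10 df) or 82% (normal).

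**Step 5: Holm against Bonferroni.** Simulation with five independent outcomes, t on 10 df and 200,000 replicates: with d = 0.5 on all five, average power per outcome is 63% under Bonferroni and 80% under Holm. With d = 0.5 on three of the five, it is 63% and 69%.

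**The case against.** The strongest reply is that no printed figure is wrong. The power sentence uses Cohen's d and speaks of outcome variables, which is ordinary language for a between-group effect, and in that sense it reproduces. It never expressly claims power for interactions. Moderation appears in a later sentence of the secondary-aims paragraph and is not itself labelled a secondary aim. Low interaction power is usual in a trial sized for a main effect. All of this stands. A reader might infer that the protocol has made an arithmetic error; the documents do not support that.

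The interaction figures also need inputs that the article does not give: the splits, a binary moderator, five comparisons (the five moderators are offered only as examples), and 0.5 SD taken as the size of the interaction. That too is fair, so the figures are illustrations. The direction does not depend on the split or the number of comparisons, because the most favourable choice of both still gives only 57%.

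A second tempting inference is that the claim also fails for the behavioral and psychosocial outcomes. The Bonferroni sentence directly follows the one on subgroup interactions and most naturally refers to them. Even on the wider reading, the result turns on the convention (63% or 82%). At the pilot-based ICC of 0.002 the t-test on 10 df gives 80%. That part can only be conditional.

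Finally, Bonferroni is a valid method. Replacing it is an improvement, not the correction of an error.

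**Conclusion.** The statement is correct for one unadjusted between-group comparison (88% or 94% at d = 0.5) and too broad for the secondary aims as a whole. For the planned interactions, power at 0.5 SD is at most 57% without adjustment, and 33% (even split) or 19% (20/80 split) with Bonferroni over five moderators. A difference in effect of 0.5 SD would thus be missed at least 43% of the time, and 67% to 81% of the time after that adjustment. These figures rest on the article's sample size, loss and ICC, and on an assumed binary participant-level moderator, assumed splits and an assumed five comparisons. The wording should be corrected, because moderation is a stated purpose of the study and its null results are easy to over-read.

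**What to change.** 1. In the sample size section, limit the statement of more than 80% power to a single between-group comparison at unadjusted two-sided alpha 0.05. Add that it does not extend to the moderator interactions, for which about 0.8 SD is detectable with 80% power at alpha 0.01 and an even split. Describe the moderator analyses as exploratory, report interaction estimates with confidence intervals, and state that a non-significant interaction is not evidence of a uniform effect.
2. In the analysis plan, replace Bonferroni with Holm, and say in the same sentence which tests form the family. Holm keeps the same family-wise error control, needs no further assumption and never rejects fewer hypotheses.

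The cost is rewording only, with no extra participants or data. The downsides are a less favourable power statement, and simultaneous confidence intervals that are less simple under Holm than under Bonferroni.

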#### Analysis plan

The primary outcome measure, change in weight from baseline over time, is assessed at six and 12 months. All measured weights will be included in the analyses. The analysis strategy is based on a conceptual framework that explicitly recognizes that both differences between individuals within clinics and between clinics may contribute to variance in weight change. Randomly assigned group (standard care versus intervention) is the main independent variable for intention-to-treat (ITT) analyses. County is a stratification variable for randomization and is expected to be balanced across intervention and standard care groups by design. Our analysis approach uses linear mixed-effect models to analyze differences between the intervention and standard care clinics allowing for within-cluster variation (participants within the same clinic) and within-individual variation (repeated measures) [132]. The model will include factors for a fixed effect for treatment and group and random effects for clinic as well as a group × time interaction term to test if the change over time in the dependent variable differs significantly for the two study groups. In addition, for primary and secondary outcomes, the model will include participant-level covariates to adjust for any baseline differences, or adjust for covariates that may relate to the outcome, including lactation, age, age at menarche, education, income, smoking status, language, socioeconomic status, race and ethnicity, height, pre-pregnancy BMI, parity, gestational gain, inter-pregnancy interval, baseline BMI, and changes in marital status and employment [2,133-139] In addition, the model will include terms to account for whole-clinic (cluster-level) variants, including Latina proportion, lactation proportion, mean age, mean education, and mean SES.

Our study design will give rise to temporally repeated measurements, and some subjects may be lost to follow up. In the primary analysis, missing weight measurements will be assumed missing at random, but diagnostic analyses will be conducted related to missing data (for example, comparing baseline characteristics of completers versus non-completers and creating propensity scores). If missing data appear to have the potential of influencing interpretation, we will also conduct multiple imputations using several different models for non-ignorable missingness. These will be used to assess the range of impact that missing data may exert on our results.

A secondary aim is to test the hypothesis that the intervention will result in a greater percentage of the women achieving their preconception weight or below at 12 months. For this analysis, a generalized linear mixed-model (binomial with a logit link) will be used for proportion at preconception weight or below at six and 12 months postpartum, including the same predictors described above. For secondary analyses comparing changes in behavioral and psychosocial variables, the effect of treatment at each time point will be investigated using the same basic linear mixed-effects model described above. In analyses of the possible differential effects of treatment on various subgroups of women, interactions between patient-level covariates (as in the main analyses) and group will be examined. A Bonferroni adjustment will be used to adjust for multiple comparisons. Also, generalized linear mixed-model analyses, as described above, will also be conducted to examine whether baseline variables moderate weight loss outcomes. Analyses of whether any effect of the intervention is mediated by differences in demographic, behavioral, and psychosocial factors will be conducted by first eliminating variables that have no impact on weight loss, then variables of interest will be entered into a final linear mixed-effects model, using both theoretical considerations to guide variable selection and the statistical strength of potential predictor variables [140].

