**Methods/Design:**

Fit Moms/*Mamás Activas* targets recruitment of 12 Women, Infants and Children (WIC) Supplemental Nutrition Program clinics with a total of 408 adult (>18 years), postpartum (<1 year) women with 14.5 kg or more weight retention or a body mass index of 25.0 kg/m^2^ or higher. Clinics are matched on size and randomly assigned within county to either a 12-month standard WIC intervention or to a 12-month WIC enhanced plus internet-based weight loss intervention. The intervention includes: monthly face-to-face group sessions; access to a website with weekly lessons, a web diary, instructional videos, and computer-tailored feedback; four weekly text messages; and brief reinforcement from WIC counselors. Participants are assessed at baseline, six months, and 12 months. The primary outcome is weight loss over six and 12 months; secondary outcomes include diet and physical activity behaviors, and psychosocial measures.

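### The primary model sentence is mis-stated and leaves open which contrast tests the hypothesis, with what clinic-level error term, and at which visit

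*Protocol article*

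**What the plan says.** All references are to the Protocol article.

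- **Outcome.** The Analysis plan states: "The primary outcome measure, change in weight from baseline over time, is assessed at six and 12 months". It then adds: "All measured weights will be included in the analyses". The first points to change scores as the dependent variable, the second to the weights themselves.
- **Model.** The mixed model is described as "allowing for within-cluster variation (participants within the same clinic) and within-individual variation (repeated measures"). The next sentence lists "a fixed effect for treatment and group and random effects for clinic as well as a group × time interaction term", and the purpose given to the interaction is "to test if the change over time in the dependent variable differs significantly for the two study groups". No other term is given a testing purpose for the primary outcome.
- **Visits.** The abstract says "The primary outcome is weight loss over six and 12 months". Study aims states that the programme "will produce significantly greater weight losses than the standard WIC at six and 12 months". Sample size calculation refers only to "power to detect a meaningful difference in weight change at 12 months".
- **Design.** Under Randomization and masking, four of the 12 clinics are crossed over. The model description does not mention them.

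**The concern.** The sentence that defines the primary model cannot be followed as written. Group is defined in the same section as standard care versus intervention, so treatment and group name one factor twice. An interaction with time is listed without time itself.

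The two possible dependent variables lead to different tests. On change scores, group × time asks whether the arm difference moves between six and 12 months, which is not the primary hypothesis. On weights it asks the right question, but a random clinic intercept cancels when a woman's baseline weight is subtracted from her 12-month weight. Variation between clinics in weight change, which is what the sizing ICC describes, then has no place in the error term unless a clinic-by-time effect is fitted.

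Two visits also share primary status, with no statement of whether one, the other or both must succeed. At stake are a sustained benefit judged by a term that cannot see it, an interval that is too narrow, and a choice of visit made after the data are seen.

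**Working it through.** **Inputs from Sample size calculation:** 12 clinics (six per arm), 34 women per clinic, 30% attrition, SD of weight change 4.5 kg, ICC 0.02 (pilot estimate 0.002), difference 2 kg, two-sided 0.05. **Assumptions not in the document:** the correlation between six- and 12-month changes, and the same SD and ICC at both visits.

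**1. The plan's own figure.**
- Completers per clinic: 34 × 0.70 = 23.8. Per arm: 6 × 23.8 = 142.8.
- Design effect: 1 + (23.8 − 1) × 0.02 = 1.456.
- SE = 4.5 × √(2 × 1.456 / 142.8) = 0.643 kg, so 2 / 0.643 = 3.11.
- Power is 80.1% with a t test on 10 clinic-level degrees of freedom, and 87.3% with individual-level degrees of freedom.

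The stated power of at least 80% is reproduced. It belongs to the between-arm difference in 12-month change, with clinic variance in change counted.

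**2. Change from baseline as dependent variable.** The interaction estimates (gap at 12 months) − (gap at six months).
- 2 kg at both visits: 2 − 2 = 0, so it rejects 5% of the time, by chance only.
- 1 kg at six and 2 kg at 12 months: the SD of a woman's change between visits is 4.5 × √(2(1 − ρ)), and its SE is that SD × √(2 × 1.456 / 142.8) = SD × 0.1428.
  - ρ = 0.6: SD 4.02, SE 0.575, ratio 1 / 0.575 = 1.74, power 35% (10 df).
  - ρ = 0.8: SD 2.85, SE 0.406, ratio 2.46, power 60%.
- 3 kg fading to 2 kg gives a difference of the same size with opposite sign. A significant result would then reflect the fading.

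**3. Weight at 0, six and 12 months as dependent variable.** Suppose within-woman correlation is modelled but clinic enters as an intercept only.
- SE used: 4.5 × √(2 / 142.8) = 0.533 kg. SE needed: 0.643 kg. Ratio: √1.456 = 1.207.
- Type I error = 2 × [1 − Φ(1.96 / 1.207)] = 2 × [1 − Φ(1.624)] = 10.4%. A simulation with 24 women per clinic gave 10.6%.
- At the pilot ICC: design effect 1 + 22.8 × 0.002 = 1.0456, type I error 5.5%.
- With clinic variance in change modelled and 10 df, simulated type I error is 5.1%.

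*Crossed-over clinics.* Assume the four clinics contribute equally to both arms with stable clinic effects, so that those effects cancel. Each of the other eight carries weight 1/6 in its arm. In units of the total variance, the clinic part is 8 × (1/36) × 0.02 = 0.00444. Relative to 2 / 142.8 = 0.01401 that is 0.317, and the inflation is 0.98 + 0.317 = 1.30 instead of 1.456. Type I error is then about 8.5%.

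**4. Two primary visits, each tested at 0.05.**
- Either suffices: familywise error from the bivariate normal is 7.8% at correlation 0.8 and 9.1% at 0.5.
- Both required: no inflation.

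**The case against.** The strongest reply is that the text, read as a whole, points to a sound analysis. The sentence before the model terms allows for repeated measures within a woman. The text says random effects, in the plural, and never says intercept; the same section recognises that clinics may contribute to variance in weight change. Group is the main independent variable and has a fixed effect, so on change scores a constant benefit would show there. The doubled factor is probably a slip for time and group. The secondary analyses take treatment effects at each visit from the same basic model. The hypothesis at six and 12 months can mean that both are required. A condensed article may also leave covariance structure and degrees of freedom to a fuller document.

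Much of this stands. A reader might infer that the model has no participant-level term, or that the primary test is invalid whichever dependent variable is meant. The documents support neither: within-woman variation is expressly allowed for, and on weights the interaction is valid if clinic-by-time is among the clinic random effects. A reader might also infer a false-positive rate of twice nominal as a property of the plan. That holds only for an intercept-only clinic effect at the planning ICC. The pilot ICC gives little inflation, and the crossed-over clinics may lower it.

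The reply does not remove what the article states: one factor named twice, time omitted, an outcome defined as change, and the test assigned to the interaction. Nor does it supply a rule for the two visits. The Bonferroni sentence follows the subgroup analyses and is not tied to the primary visits.

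**Conclusion.** The concern holds as a mis-stated primary model that permits materially different tests, not as proof that the primary test is invalid.

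- On change scores, the interaction misses a constant 2 kg benefit by construction; the 12-month group effect is what tests the hypothesis.
- On weights, the target is right. The error term is too small only if clinic-by-time is left out: type I error about 10% at ICC 0.02 in a parallel six-versus-six design, about 8.5% if the crossed-over clinics cancel as assumed, and about 5.5% at ICC 0.002.
- With no rule for the two visits, familywise error is about 8% to 9% if either suffices (assumed correlation 0.8 to 0.5), and not inflated if both are required.

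The 12-month difference in change, with clinic variance in change counted, is the contrast the sample size assumes and has about 80% power with 10 df.

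**What to change.** Reword the model paragraph before data are analysed:

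1. State that the dependent variable is weight at baseline, six and 12 months.
2. Replace the doubled factor with group and categorical time, plus group × time, and include county.
3. State a participant-level term or a within-woman covariance, and clinic and clinic-by-time random effects, with cluster-level degrees of freedom (for example, Kenward-Roger).
4. Code the four crossed-over clinics by period, so that arm can vary within clinic and those clinics have a defined place in the random structure.
5. Name the between-arm difference in change from baseline to 12 months as the primary contrast.
6. State the rule for six months: for example, tested only if 12 months is significant, or both visits required.

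The cost is wording, a somewhat wider interval than an intercept-only clinic effect would give, and a six-month claim that becomes conditional. If both visits are required instead, power for joint success is below that for 12 months alone and should be checked.

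### The primary test is group × time, but no covariate × time terms are stated, so time-constant covariates leave the tested effect essentially unadjusted

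*Protocol article*

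**What the plan says.** All of this stands in the Analysis plan section of the protocol article.

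- **Outcome and data.** "The primary outcome measure, change in weight from baseline over time, is assessed at six and 12 months". The next sentence adds: "All measured weights will be included in the analyses".
- **Tested term.** The linear mixed model has a "group × time interaction term to test if the change over time in the dependent variable differs significantly for the two study groups".
- **Participant-level covariates.** The plan states, for both tiers of outcome: "the model will include participant-level covariates to adjust for any baseline differences, or adjust for covariates that may relate to the outcome". Seventeen items follow. Most are fixed at baseline (age, height, parity, pre-pregnancy BMI and so on), but the list ends with "inter-pregnancy interval, baseline BMI, and changes in marital status and employment".
- **Clinic-level covariates.** "the model will include terms to account for whole-clinic (cluster-level) variants, including Latina proportion, lactation proportion, mean age, mean education, and mean SES".
- **Secondary outcomes.** Behavioral and psychosocial changes are compared at each time point "using the same basic linear mixed-effects model described above".

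No covariate × time term is mentioned for either covariate set. Where the section wants an interaction it names it: group × time for the main test, and covariate × group for subgroups.

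**The concern.** A covariate that does not change over time, entered as a main effect, raises or lowers a woman's weight by the same amount at every visit. It explains who is heavier, not who loses more. A group × time test concerns only who loses more, so such a covariate has nothing to act on there. The plan gives the covariates a purpose that the stated model does not deliver for its primary test.

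This matters more than usual in this trial. Only 12 clinics are randomized, and Randomization and masking stratifies by county alone, deciding against stratifying by ethnicity and pre-pregnancy BMI. Both are on the covariate list, so model adjustment is the remaining protection against chance imbalance in them. The trial could report as covariate-adjusted an estimate that is in substance the unadjusted one.

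**Working it through.** **1. Algebra, weight as response.** For woman i at visit t, with group g and time-constant covariate x:

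weight(i,t) = a(t) + b·g(i) + c(t)·g(i) + d·x(i) + random terms.

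The group × time effect at 12 months is c(12) − c(0). Subtracting baseline from 12 months gives

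weight(i,12) − weight(i,0) = [a(12) − a(0)] + [c(12) − c(0)]·g(i) + error.

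The term d·x(i) has cancelled. It survives only if d depends on the visit, that is, with covariate × visit.

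**2. Numerical check.** Twelve clinics of 34 women were simulated at 0, 6 and 12 months with a true 12-month effect of -2 kg. Assumed: arms differ by 0.5 SD on x, and x shifts 12-month change by -1 kg per SD. Group × time estimates at 12 months, averaged over eight data sets:

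| Model | Complete data | About 30% dropout |
|---|---|---|
| No covariate | -2.34 kg (SE 0.436) | -1.93 kg |
| x as main effect | -2.34 kg (SE 0.436) | -1.92 kg |
| x and x × visit | -1.81 kg (SE 0.446) | -1.33 kg |

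With complete data the first two rows agree to within 1e-12. In exact generalized least squares the same held under random-intercept and unstructured covariance, with or without four crossed-over clinics. With dropout, the main effect moved the estimate by at most 0.03 to 0.10 kg (SE 0.49 to 0.91).

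**3. Change from baseline as response.** Now x can act on the group effect at a visit. In the same simulation the 12-month contrast went from -2.34 to -1.94 kg, and the average over visits from -1.78 to -1.38 kg. The adjustment at 12 months falls short of that with x × visit (-1.81 kg) because one slope is shared by both visits. The group × time term, which is now only the 6-to-12-month difference, stayed at -1.11 kg with and without x.

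**4. Time-varying covariates.** An employment-like covariate that changed between visits moved the group × time estimate by up to 0.29 kg with complete data and 0.37 kg with dropout.

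**5. Size of the uncorrected imbalance.** It equals imbalance in SD × kg of change per SD. The simulated case is 0.5 × 1 = 0.5 kg, a quarter of the 2 kg target, but 0.5 SD is a large imbalance. If a covariate had the same ICC as the sample size section uses (0.02, an assumption here), the design effect at enrolment is 1 + 33 × 0.02 = 1.66. The chance SD of the arm difference, with 6 × 34 = 204 women per arm, is √(2 × 1.66/204) = 0.128 SD. With the protocol's SD of 4.5 kg:

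- 1 kg per SD (R² = 1/4.5² = 5%): 0.13 kg
- R² 10% (√0.10 × 4.5 = 1.42 kg per SD): 0.18 kg
- R² 20% (√0.20 × 4.5 = 2.01 kg per SD): 0.26 kg

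These are one-standard-deviation imbalances.

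**6. Precision.** First the protocol's own figure. Retained per clinic: 34 × 0.7 = 23.8. Design effect: 1 + 22.8 × 0.02 = 1.456. Effective n per arm: 6 × 23.8/1.456 = 98.1. SE: 4.5 × √(2/98.1) = 0.643 kg. Noncentrality: 2/0.643 = 3.11. Power on 10 df is 80.1%, which reproduces the stated 80%. If covariates explained a share R² of the variance of change, the SE would shrink by √(1 − R²):

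| R² (assumed) | 10 df | 5 df |
|---|---|---|
| 0 | 80.1% | 70% |
| 0.10 | 84.0% | 75% |
| 0.20 | 87.9% | 79% |

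The 5 df column shows what happens if all five clinic-level terms act on the tested effect: 12 − 2 − 5 = 5, ignoring the crossed-over clinics.

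**7. Dropout.** With 30% loss depending on a binary covariate worth 2 kg in opposite directions by arm (20/40% against 40/20%, an assumed and deliberately unfavourable pattern), main-effect adjustment left -0.28 kg that covariate × visit removed (80 simulated trials, Monte Carlo SE 0.013).

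**The case against.** The strongest reply is that the article never says the covariates are main effects only. It is a condensed account, and an unseen analysis plan may cross them with visit. That stands as a limit: main effects are inferred from the absence of any covariate × time term in a section that names its other interactions.

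Second, the primary outcome is called change from baseline and the trial is powered on 12-month change. If change is the response and the group effect at a visit is tested, main-effect covariates do adjust it. This also stands, but it is not the test the section names. Under that response the named group × time term is again unaffected, and it is not even the 12-month effect the trial is powered for.

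Third, changes in marital status and employment are not baseline constants, and Supporting measures describes follow-up data on smoking, job status and breastfeeding. Entered as time-varying, these would move the interaction. A reader might therefore infer that the covariates adjust nothing at all. The document does not support that; the claim is exact only for time-constant covariates with complete follow-up.

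Fourth, full crossing is not cheap: 22 listed covariates over two follow-up visits would add at least 44 coefficients, and crossing the clinic-level terms could lower power below the unadjusted figure. This is right, and it shapes the fix.

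**Conclusion.** The point holds in a limited form. As stated, the model tests group × time with no covariate × time term. With weight at all three visits as response and baseline covariates as main effects, the tested effect is unadjusted with complete data and nearly so at 30% attrition. The stated aim of adjusting for baseline differences is not met for the primary test.

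Two stronger readings are tempting. One is that the primary result would be biased: it would not be with complete data, because randomization protects the unadjusted estimate on average. The other is that the secondary linear models fail in the same way: they refer to the treatment effect at each time point, which may be a visit-specific contrast that main effects can adjust, so the point applies to them only if they are tested by group × time.

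The cost is uncorrected chance imbalance (0.13 to 0.26 kg at one standard deviation under the assumptions above, 0.5 kg in the large imbalance simulated), a forgone gain from 80.1% to 84-88% power if R² is 10-20%, and little correction of covariate-related dropout. These sizes rest on assumed imbalance, R², ICC and dropout patterns and are illustrations. That the covariate cancels is algebra and does not depend on them.

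**What to change.** State the response and the tested contrast in the Analysis plan, then choose one of two forms:

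1. Model 6- and 12-month change from baseline and make the group effect at each visit (12 months, 6 months) the tested contrast, with participant-level baseline covariates and their visit interactions.
2. Keep weight at all visits and the group × visit test, and add covariate × visit terms for a short prespecified set of prognostic participant-level baseline covariates.

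Do not cross all five clinic-level terms with visit; 12 clinics cannot support them. Say which covariates, if any, enter as time-varying. Use the same form for the secondary linear models if they are tested by group × time.

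The change is to wording only and needs no new data. The cost is a few extra coefficients per retained covariate, which is why the set should be short.
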